**Expected adverse events**

　The expected adverse events in this study are as follows: refer to the package insert for updated information.

Side effects of aspirin

(1) Significant adverse reactions

1. Shock and anaphylaxis (incidence unknown): Shock or anaphylaxis (dyspnea, generalized flushing, angioedema, urticaria, etc.) may occur. Patients should be carefully monitored, and if any abnormalities are observed, administration should be discontinued and appropriate measures should be taken.

2. Intracranial hemorrhage such as cerebral hemorrhage,(initial symptoms: headache, nausea/vomiting, disturbed consciousness, hemiplegia, etc.) may occur. Patients should be carefully monitored, and if such symptoms are observed, administration should be discontinued and appropriate measures taken. Pulmonary, gastrointestinal, epistaxis and fundus hemorrhage may occur. Patients should be carefully monitored, and if such symptoms are observed, administration should be discontinued and appropriate measures taken.

3. Toxic epidermal necrolysis (TEN), oculomucocutaneous syndrome (Stevens-Johnson syndrome), and exfoliative dermatitis may also occur. Patients should be carefully monitored, and if such symptoms are observed, administration should be discontinued and appropriate measures should be taken.

4. Aplastic anemia, thrombocytopenia, and leukopenia: Patients should be carefully monitored, and if any abnormalities are observed, administration should be discontinued and appropriate measures should be taken.

5. Asthma attacks: It may induce asthmatic attacks.

6. In hepatic function disorders and jaundice with significant elevations in hepatic function disorder, AST (GOT), ALT (GPT and gamma-GTP) may occur. Patients should be carefully monitored, and if any abnormal findings are observed, appropriate measures, such as discontinuation of administration, should be taken.

7. Peptic ulcers, small and large intestine ulcers: Peptic ulcers such as gastric and duodenal ulcers with melena may occur. Small- and large-intestinal ulcers associated with gastrointestinal bleeding and perforation may also occur. Patients should be carefully monitored, and if any abnormalities are observed, the administration should be discontinued and appropriate measures should be taken.

(2) Since no domestic survey has been conducted to clarify the indications for adverse-reaction drugs and the frequency of adverse reactions in terms of administration and dosage, it is based on the frequency of adverse reactions caused by aspirin-based preparations used as antipyretic analgesics and anti-inflammatory agents.

|  | More than 5% or frequency unknown | 0.1~ <5% | <0.1% |
| --- | --- | --- | --- |
| Digestive system | Gastrointestinal disorders, vomiting, abdominal pain, heartburn, constipation, diarrhea, esophagitis, lip swelling, hematemesis, nausea | Nausea, anorexia, stomach discomfort |  |
| Hypersensitivity ^1)^ | Urticaria | Rash, edema |  |
| Hematologic ^2)^ |  |  | Anemia, decreased platelet function (prolonged bleeding time) |
| Skin | Pruritus, rash, wheal, sweating |  |  |
| Psychoneurological ^3)^ | Dizziness, agitation | Headache |  |
| Liver | Increased AST (GOT)  ALT (GPT) |  |  |
| Kidney |  |  | Kidney damage |
| Cardiovascular | Hypotension, vasculitis | Epigastric pain |  |
| Respiratory system | Bronchitis | Rhinitis |  |
| Sensory organ | Keratitis and conjunctivitis | Tinnitus, hearing loss |  |
| Miscellaneous ^4)^ | Hyperpnea, metabolic acidosis | Malaise | Hypoglycemia |

1. If any symptom occurs, the therapy should be discontinued.

2. If any abnormality is observed, osimertinib should be discontinued, and appropriate measures should be taken.

3. If any symptoms are observed, the dose should be reduced or administration should be discontinued.

4. Dose reduction or discontinuation (blood concentration may be markedly elevated).

In the foreign post-marketing surveillance of drugs used as antiplatelet agents, the number of patients with adverse reactions was 73 (87 adverse reactions) of the 2739 patients surveyed, and the incidence of adverse reactions was 2.67%. According to the classification of adverse drug reactions according to organs, gastrointestinal disorders (gastritis, gastrointestinal bleeding, ulcers, etc.) were the most common (2.81%), followed by hemorrhage/coagulopathy (hematoma, retinal hemorrhage, etc.) (0.15%), hypersensitivity (rash) (0.07%), psychiatric nervous system disorders (dizziness), and hematological disorders (anemia) were all 0.04%.

# **8.** **Observation and examination items**

Study period of patients

The study period for each patient is as follows;

| (1) Duration of study participation | Time from informed consent to the end of the observation period |
| --- | --- |
| (2) Observation period | Time from the date of registration to the last observation day (3 months after surgery) |

Observation/examination items and treatment information to be reported

The items to be investigated in this study are as follows:

At the time of registration

| Patient background | | |
| --- | --- | --- |
| Date of birth | (yyyy/mm/dd) | |
| Date of admission | (yyyy/mm/dd) | |
| Date of informed consent | (yyyy/mm/dd) | |
| Age at the time of consent |  | |
| Sex |  | |
| History of stroke | Subarachnoid hemorrhage, hemorrhagic stroke other than subarachnoid hemorrhage, ischemic stroke | |
| Comorbidity/lifestyle | Hypertension, diabetes mellitus, dyslipidemia, smoking habits | |
| Other concomitant medication | Antihypertensive, antidiabetic, dyslipidemic, anticoagulant (drug name) | |
| Pre-morbid mRS | 0, 1, 2, 3 | |
| Vital signs (on arrival at hospital) | | |
| Blood pressure | Systolic blood pressure, diastolic blood pressure (mmHg). | |
| Respiratory rate | (/min of times) | |
| Heart rate | (/min of times) | |
| Body temperature | (℃) | |
| Neurological findings on admission | | |
| Glasgow coma scale | E | 1, 2, 3, 4 |
|  | V | 1, 2, 3, 4, 5 |
|  | M | 1, 2, 3, 4, 5, 6 |
|  | Total score | 3, 4, 5, 6, 7, 8, 9, 10, 11, 12, 13, 14, 15 |
| Subarachnoid hemorrhage severity | | |
| WFNS class | I, II, III, IV, V | |
| Blood tests | | |
| Blood count | Hb, Plt | |
| Biochemical examination | Glu, LDL-chol, HbA1c, BNP, Alb | |
| Clotting marker | D-dimer | |
| Imaging studies | | |
| Modified Fisher grade | 0, 1, 2, 3, 4 | |
| Intraparenchymal brain hematoma | Yes (maximum diameter:), no | |

At the time of surgery

| Cerebral aneurysm information | | | | | |
| --- | --- | --- | --- | --- | --- |
| Prior treatment of the cerebral aneurysm | Yes (clipping, other), no | | | | |
| Site | ICA-paraclinoid, ICA-Pcom, ICA-ant.choroidal, ICA-bif, MCA M1, MCA bif, A1, Acom, distal ACA, VA, VA-PICA, BA trunk, BA-SCA, BA bif, PCA, others (ant. circulation), others (post. circulation) | | | | |
| Cerebral aneurysm geometry (angiography) | Maximal diameter (mm) ∗ does not include small bleb | | | | |
|  | Dome diameter (mm) | | | | |
|  | Neck diameter (mm) | | | | |
|  | Neck proximal mother vessel diameter (mm). | | | | |
|  | Incorporated branch (present, absent) | | | | |
| Characteristics of cerebral aneurysms | Thrombosed (present, absent), bleb (present, absent), others (). | | | | |
| Surgical procedures before cerebral aneurysm embolization | None, ventricular drainage, spinal drainage, decompressive craniectomy, hematoma evacuation, or other | | | | |
| Cerebral aneurysm embolization information | | | | | |
| Day of surgery | Sheath insertion time | | | (yyyy/mm/dd/HH/mm) | |
|  | Final intracranial angiographic time | | | (yyyy/mm/dd/HH/mm) | |
| Surgeon information | JSNET specialist information | Non-specialists, specialists, teaching physicians | | | |
|  | Number of surgical experiences for cerebral aneurysm | 0-9, 10-19, 20-39, 40-59, 60-99, 100  More than | | | |
| Surgical information | Approach site | | Inguinal, brachial, radial, carotid | | |
|  | Intraoperative heparin dose | | Total unit | | |
|  | ACT | | Control | | (sec) |
|  |  | | Maximum value | | (sec) |
|  | Use of a balloon-guiding catheter | | Yes, no | | |
|  | Use of balloon catheters other than neck modeling | | Yes (dilated and absent in blood vessels), no | | |
|  | Assistive techniques | | Use of DAC | | Yes, no |
|  |  |  | BAT | | Yes, no |
|  |  |  | SAT | | Yes, no |
|  |  |  | DCT | | Yes, no |
|  | Raymond Roy class | | I, II, IIIa, IIIb | | |
|  | Immediate postoperative embolization | | CO, NR, BF | | |
|  | Coil protrusion grade | | Yes (I, II, III), no | | |
|  | Intraoperative rupture | | Yes, no  (detailed description) | | |
|  | Intraoperative thrombus | | Yes, no  (detailed description)  Occluded vessels in the final angiography  Yes, no  Thrombus in final angiography  Yes, no | | |
|  | Other intraoperative complications | | Yes, no  (detailed description) | | |

Observation period (MRI: 6-48 h after surgery; CT, 48 h after surgery)

| MRI examination (6-48 h after surgery). | | | | | | | |
| --- | --- | --- | --- | --- | --- | --- | --- |
| Date and time of survey | | | (yyyy/mm/dd/HH/mm) | | | | |
| DWI | Presence of ischemic lesions | | | | | Yes, no | |
|  | Presence of symptomatic ischemic lesions | | | | | Yes (site, size), no | |
|  | Number of ischemic lesions in the area of the parent artery in the aneurysm | | | | | 0 – 4 mm |  |
|  |  | | | | | 5 – 9 mm |  |
|  |  | | | | | 10 – 14 mm |  |
|  |  | | | | | 15 mm or higher |  |
|  | Number of ischemic lesions other than the area of the aneurysm's parent artery | | | | | 0 – 4 mm |  |
|  |  | | | | | 5 – 9 mm |  |
|  |  | | | | | 10 – 14 mm |  |
|  |  | | | | | 15 mm or higher |  |
| MRA | Degree of aneurysm embolization | | | | | CO, NR, BF | |
|  | Newly occluded vessels | | | | | Yes, no | |
| CT examination (within 48 h after surgery) | | | | | | | |
| Date and time of survey | | | (yyyy/mm/dd/HH/mm) | | | | |
| Increased subarachnoid hemorrhage | | Yes, no | | | | | |
|  | | Modified Fisher grade | | | 0, 1, 2, 3, 4 | | |
| Increase in cerebral parenchymal blood species | | Yes, no | | | | | |
|  | | Size (maximum diameter) | | | | | |
| New parenchymal brain hematoma | | Yes (maximum diameter), no | | | | | |
| Increased hydrocephalus | | Yes, no | | | | | |
| Appearance of cerebral hemorrhage along tube tract  (only for cases with ventricular drainage) | | | | Yes (maximum diameter), no | | | |
| Surgical procedure after cerebral aneurysm treatment (during period after surgery to MRI scan), (multiple responses possible) | | | | | | | |
| Yes (ventricular drainage, spinal drainage, decompressive craniectomy, hematoma evacuation, cerebral aneurysm neck clipping, other), no | | | | | | | |
| Date of enforcement | | | | (yyyy/mm/dd) | | | |
| Antithrombotic therapy (during the period after surgery to MRI scan) | | | | | | | |
| Yes (detail), no | | | | | | | |
| Worsening of neurologic manifestations (during the period after surgery to MRI scan) | | | | | | | |
| Yes (disturbed consciousness, paralysis, sensory disturbance, aphasia, hemispatial neglect, others [details]), no | | | | | | | |

Observation period (14 days after surgery), acceptable range: ±2 days

| Day of investigation |
| --- |

| Day of investigation | (yyyy/mm/dd) |
| --- | --- |

| Subject information |
| --- |

| Continuous intravenous Nicardipine Hydrochloride therapy | Yes, no |
| --- | --- |
| IV Fasudil Hydrochloride Hydrate therapy | Yes, no |
| IV Ozagrel Sodium therapy | Yes, no |
| New cerebral infarction due to cerebral vasospasm | Yes, no |
| Endovascular treatment for symptomatic cerebral vasospasm. | Yes, no |
|  | Procedural details (), date, and time (). |

| Other antithrombotic therapies present |
| --- |
| Yes (detail), no |
| Safety information |

| Serious adverse event | Yes (if "yes", report details of "event/adverse event/occurrence of re-treatment"), no |
| --- | --- |
| Retreatment | Yes (if "yes", report details of "event/adverse event/occurrence of re-treatment"), no |

| CT |
| --- |

| Date and time of survey | (yyyy/mm/dd) |
| --- | --- |

| Increased subarachnoid hemorrhage | Yes, no | | |
| --- | --- | --- | --- |
|  | Modified Fisher grade | | 0, 1, 2, 3, 4 |
| Increase in cerebral parenchymal blood species | Yes (maximum diameter), no | | |
| New parenchymal brain hematoma | Yes (maximum diameter), no | | |
| Increased hydrocephalus | Yes, no | | |
| Appearance of cerebral hemorrhage along tube tract (only for cases with ventricular drainage) | | Yes (maximum diameter), no | |
| Surgical procedures after cerebral aneurysm treatment (multiple responses possible) | | | |
| Yes (ventricular drainage, spinal drainage, decompressive craniectomy, hematoma evacuation, cerebral aneurysm neck clipping, other), no | | | |

| Date of enforcement | (yyyy/mm/dd) |
| --- | --- |

| Worsening neurologic findings |
| --- |

| Yes (disturbed consciousness, paralysis, sensory disturbance, aphasia, hemispatial neglect, others (details)), no |
| --- |

Observation period (3 months after surgery) Acceptable range: ±14 days

| Day of investigation | |
| --- | --- |
| Day of investigation | (yyyy/mm/dd) |
| Subject information | |
| mRS | 0, 1, 2, 3, 4, 5, 6 |
| Shunt surgery for secondary hydrocephalus | Yes, no |
|  | Date (yyyy/mm/dd) |
|  | Ventriculoperitoneal shunt; lumbar peritoneal shunt; other |
| Safety information | |
| Serious adverse event | Yes (if "yes", report details of "event/adverse event/occurrence of re-treatment"), no |
| Retreatment | Yes (if "yes", report details of "event/adverse event/occurrence of re-treatment"), no |

Events, adverse events, and re-treatment occurrences (multiple responses possible)

| Event, adverse event, or retreatment | | |
| --- | --- | --- |
| Date of incident | (yyyy/mm/dd) | |
| Stroke events | | |
| Ruptured cerebral artery aneurysm | Treated aneurysm, otherwise (detail) | |
|  | WFNS Grade (I, II, III, IV, V) | |
|  | Retreatment: yes or no | |
|  | Date of retreatment | (yyyy/mm/dd) |
|  | Retreatment method | Craniotomy, endovascular treatment |
|  | Treatment outcome | CO, NR, BF |
| Other hemorrhagic stroke | Yes, no | |
|  | Details () | |
| Ischemic stroke | Yes, no | |
|  | Details () | |
| Other bleeding events | | |
| Significant hemorrhage by ISTH criteria  (Intracranial hemorrhage is described in the stroke event.) | Yes, no  Details () | |
| Other adverse events | Yes; details (), no | |

| Observation items    Time of implementation | Registration | Observation period | | | |  |
| --- | --- | --- | --- | --- | --- | --- |
|  | Preoperative | Intraoperative | Within 2 days after surgery | 14 days (±2 days) after surgery | 3 months (±14 days) after surgery | Time of event/event |
| Obtaining informed consent, registering  Allocation | ○ | − | − | − | − | − |
| Basic Information | ○ |  |  |  |  |  |
| Vital signs | ○ |  |  |  | − | − |
| Blood test | ○ |  | ○ | ○ |  |  |
| General blood chemistry | ○ |  | ○ | ○ |  |  |
| Clotting marker | ○ |  |  |  |  |  |
| Neurologic findings | ○ |  | ○ (during the period after surgery to MRI) | ○ | ○ | ○ |
| Daily life independence | ○ | − | − | − | ○ | ○ |
| Information on surgical technique | − | ○ | − | − | − | − |
| Images (MRI) | − | − | ○ (within 6-48 h after surgery) | − | − | − |
| Images (CT) | ○ | − | ○ (within 48 h after surgery) | ○ | − | − |
| Event | From time to time | | | | | − |
| Serious adverse event |  |  |  |  |  | − |
| Retreatment |  |  |  |  |  | − |

Event definitions, etc.

Antiplatelet agents administered before surgery that meet the exclusion criteria

　Ticlopidine, clopidogrel, prasugrel, cilostazol, aspirin

・Subarachnoid hemorrhage

　It is diagnosed by recognizing the hemorrhage in the subarachnoid space by head CT and MRI or by recognizing bloody cerebrospinal fluid by lumbar puncture.

Subarachnoid hemorrhage severity grading (WFNS grading)

　WFNS subarachnoid hemorrhage severity grading (1983) (see table below). The degree of subarachnoid hemorrhage on imaging is determined using a Modified Fisher grading system.

WFNS grade

| Severity | GCS scoring | Major focal neurologic symptoms (aphasia or hemiplegia) |
| --- | --- | --- |
| Grade I | 15 | Absent |
| Grade II | 14-13 | Absent |
| Grade III | 14-13 | Present |
| Grade IV | 12-7 | Present or absent |
| Grade V | 6-3 | Present or absent |

Glasgow coma scale (GCS, 1974)

| Large classification | Small classification | Score |
| --- | --- | --- |
| A. Eyes open | Spontaneously  To speech  To pain  No response | E4  E3  E2  E1 |
| B. Verbal responses | Oriented to time, person, and place  Confused  Inappropriate words  Incomprehensible sounds  No respnse | V5  V4  V3  V2  V1 |
| C. Best response to exercise | Obeys command  Moves to localized pain  Flex to withdraw from pain  Abnormal flexion  Abnormal extension  No response | M6  M5  M4  M3  M2  M1 |

Modified Fisher grading system

| 0 | No SAH or intraventricular hemorrhage |
| --- | --- |
| 1 | Focal or diffuse thin SAH without intraventricular hemorrhage |
| 2 | Focal or diffuse thin SAH with intraventricular hemorrhage |
| 3 | Focal or diffuse thick SAH without intraventricular hemorrhage |
| 4 | Focal or diffuse thick SAH with intraventricular hemorrhage |

・Measurement of cerebral aneurysm

1. Maximal diameter: Maximal diameter of cerebral aneurysm (excluding small projections and bleb)
2. Dome diameter: Cerebral aneurysm diameter parallel to the neck measured by the working angle (excluding small processes and blebs).
3. Neck diameter: Neck diameter measured at working angle

・Determination of the degree of embolization of cerebral aneurysms

　Based on the findings of the immediate postoperative angiography, the following classification is used to determine the results.

| Classification | Definitions |
| --- | --- |
| CO (complete) | Contrast does not flow into the aneurysm at all |
| NR (residual neck) | Contrast medium flow only near the neck |
| BF (partial obstruction) | Flow of contrast medium into the dome |

Raymond-Roy (2015)

| Classification | Definitions |
| --- | --- |
| Class I | Complete obliteration |
| Class II | Residual neck |
| Class IIIa | Residual aneurysm with contrast within coil interstices |
| Class IIIb | Residual aneurysm with contrast along aneurysm wall |

According to the findings of the immediate postoperative angiography, the degree of deviation of the coil is judged by the following classification.

Coil protrusion grade (2011)

| Classification | Definitions |
| --- | --- |
| Grade I | Loop or coil protrudes into the main lumen less than half of parent artery diameter. |
| Grade II | Coil protrudes into the main lumen exceeding more than half of parent artery diameter. |
| Grade III | Loop protrudes into the main lumen exceeding more than half of parent artery diameter. |

・Daily life independence

Modified Rankin Scale (mRS)

| Grade | Description |
| --- | --- |
| 0 | No symptoms at all |
| 1 | No significant disability despite symptoms; able to carry out all usual duties and activities |
| 2 | Slight disability; unable to carry out all previous activities, but able to look after own affairs without assistance |
| 3 | Moderate disability; requiring some help, but able to walk without assistance |
| 4 | Moderately severe disability; unable to walk without assistance and unable to attend to own bodily needs without assistance |
| 5 | Severe disability; bedridden, incontinent and requiring constant nursing care and attention |
| 6 | Dead |

Medical history and lifestyle habits.

|  | Definitions |
| --- | --- |
| Subarachnoid hemorrhage | Subarachnoid hemorrhage due to ruptured cerebral aneurysm not targeted in this study |
| Hemorrhagic stroke | Focal neurologic symptoms and confirmed intracranial hemorrhage by head CT or MRI |
| Ischemic stroke | Focal neurologic symptoms and confirmed cerebral infarction by head CT or MRI |
| High blood pressure | Any of the following criteria met within the three months prior to treatment: systolic blood pressure of 140 mmHg or higher, diastolic blood pressure of 90 mmHg or higher, or the use of antihypertensive medication to lower blood pressure. |
| Diabetes mellitus | Any of the following criteria met within the three months before treatment: fasting blood glucose of 126 mg/dL or higher, random blood glucose of 200 mg/dL or higher, HbA1c of 6.5% or higher, use of hypoglycemic agents, or a previous diagnosis of diabetes by a medical institution. |
| Dyslipidemia | Any of the following criteria met: LDL cholesterol of 140 mg/dL or higher, HDL cholesterol less than 40 mg/dL, triglycerides of 150 mg/dL or higher, or the use of lipid-lowering agents. |
| Smoking habit | Those who have a smoking habit of one or more cigarettes per day on average within 1 year before treatment. |

・Stroke events

　The following events occurring between surgery and 14 ± 2 days after surgery are defined as stroke events in this study:

|  | Definitions |
| --- | --- |
| Postoperative rupture of cerebral aneurysm | Symptomatic subarachnoid or intracerebral hemorrhage due to rupture　cerebral aneurysm after surgery diagnosed by CT or MRI. When asymptomatic or minimal headache occurs, the decision should be made with caution. WFNS Grade, presence or absence of retreatment, and treatment modalities should also be recorded. |
| Transient ischemic attack | Transient episodes of neurological dysfunction resulting from focal cerebral or retinal ischemia without evidence of acute infarction. Episodes of neurologic dysfunction should resolve within at least 24 h. |
| Ischemic stroke | Those with focal neurological symptoms lasting more than 24 h and confirmed ischemic by head CT or MRI. |
| Hemorrhagic stroke | Symptomatic subarachnoid and intracerebral hemorrhage without rupture of target cerebral aneurysms after surgery diagnosed by CT or MRI. This is not the case if the symptom is only a headache and not accompanied by other objective neurological symptoms. |

The above transient ischemic attack and ischemic stroke are combined to define a global ischemic event.

・Bleeding events

The following events that fall under "major bleeding" according to ISTH criteria are included in the "bleeding events" of this study.

1. Fatal bleeding

2. Symptomatic hemorrhage (intracranial, intrathecal, intraocular, retroperitoneal, intraarticular or intrapericardial, or intramuscular hemorrhage with muscular compartment syndrome) at critical sites or organs.

3. Bleeding resulting in a decrease in Hb level of 20 g/L or higher, bleeding leading to whole blood transfusion, or transfusion of two or more units of red blood cells.

・Cause of death

| Cerebral aneurysm death | Death from rupture of a cerebral aneurysm or from events directly related to a cerebral aneurysm |
| --- | --- |
| Death from stroke | Death from ischemic stroke and hemorrhagic stroke due to causes other than cerebral aneurysm |
| Other deaths | Death from causes other than cerebral aneurysm and stroke |
| Unknown | Death from unknown causes |

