# **7.** **Endpoint**

## **7-1.** **Items related to the evaluation of efficacy**

　Primary outcomes

1) Incidence rate of intraoperative thrombotic complications

It is defined as the proportion of patients with evidence of cerebral angiographically evident thrombus formation in the vicinity of the aneurysm neck or parent artery during surgery.

2) Incidence rate of symptomatic ischemic lesions on MRI diffusion-weighted imaging (DWI) evaluated by the Independent Review Committee (IRC)

It is defined as the percentage of patients with acute-phase ischemic lesions on MRI-DWI performed 6–48 h postoperatively and with concordant neurologic findings.

Key secondary outcomes

1) Incidence rate of all bleeding events within 14 days of enrollment

As a basic protocol, a head CT is performed within 48 h postoperatively and at 14±2 days postoperatively. Additionally, imaging evaluations were conducted as required. The incidence rate of all bleeding events is defined as the percentage of patients with a ruptured aneurysm (symptomatic subarachnoid or intracerebral hemorrhage due to rupture of an aneurysm of interest), a hemorrhagic stroke (symptomatic subarachnoid and intracerebral hemorrhage not due to rupture of target aneurysm, or the proportion of patients who experienced "major hemorrhage" according to ISTH criteria within 14 days post-registration.

2) Incidence rate of cerebral ischemic events in the first 14 days after MRI

The basic protocol is head CT performed within 6–48 h after surgery and 14 ± 2 days after surgery. This is defined as the percentage of patients with transient ischemic attack within 14 ± 2 days after MRI (neurological symptoms lasting less than 24 h with or without imaging findings) or ischemic stroke (focal neurological symptoms lasting more than 24 h and ischemic lesions confirmed by head CT or MRI) during the study period.

Other secondary outcomes

1) Incidence rate of symptomatic ischemic lesions in MRI-DWI evaluated by INV.

2) mRS at 3 months

Assessment is based on mRS scoring 3 months after the onset of subarachnoid hemorrhage.

　Exploratory outcomes

1) Ischemic lesions on MRI-DWI (number and size: 0–4 mm, 5–9 mm, 10–14 mm, 15 mm or greater, categorized as IRC or INV)

2) Incidence rate of cerebral hemorrhage along the tube tract for ventricular drainage on CT scans in the first 14 days after EVT.

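### The event form routes intracranial bleeds to a stroke item that the protocol defines more narrowly than the ISTH bleeding component, so some bleeding endpoint events may go unrecorded or be recorded inconsistently

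*Protocol*

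**What the plan says.** Four texts in the Protocol bear on the same bleed.

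- **Endpoint (7-1, key secondary outcome 1).** Patients count if they have a rupture of the target aneurysm, a hemorrhagic stroke, or an ISTH major bleed. The last component reads: "the proportion of patients who experienced 'major hemorrhage' according to ISTH criteria within 14 days post-registration". It has no exception for intracranial bleeding.
- **ISTH definition (Section 8, bleeding events).** The critical-site criterion begins "Symptomatic hemorrhage (intracranial, intrathecal, intraocular, retroperitoneal, intraarticular or intrapericardial", with no anatomical limit on intracranial and no headache rule. Events that meet the ISTH criteria "are included in the 'bleeding events' of this study".
- **Stroke definition (Section 8, stroke events).** Hemorrhagic stroke is "Symptomatic subarachnoid and intracerebral hemorrhage without rupture of target cerebral aneurysms after surgery diagnosed by CT or MRI". The definition adds: "This is not the case if the symptom is only a headache and not accompanied by other objective neurological symptoms".
- **Event form (Section 8).** The ISTH item carries the note "Intracranial hemorrhage is described in the stroke event". Under stroke events, the two items for bleeding are a ruptured aneurysm item and "Other hemorrhagic stroke", the latter with a yes/no box and an open details field.

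Section 14-3 analyses this outcome in the mITT set. Non-inferiority is concluded if the upper limit of the 95% confidence interval for the difference (aspirin minus placebo) is below 10%.

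**The concern.** The endpoint uses the broad ISTH notion of intracranial hemorrhage. The form closes the ISTH item to such bleeds and sends them to an item whose name the protocol defines more narrowly. A site that follows the form note and the stroke definition to the letter can answer no on both items for a bleed that 7-1 counts.

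At stake is the trial's main safety comparison. In a superiority test, missed events usually cost power. In a non-inferiority test on a risk difference they shrink the difference and make the favourable conclusion easier to reach. Section 1 raises hemorrhagic complications of ventricular or spinal drainage as a worry with antiplatelet treatment, and the Section 8 forms record drainage and decompressive craniectomy. Extra-axial bleeding is therefore plausible in this population, although Section 1 does not name it.

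**Working it through.** **Step 1: follow each type of bleed through the texts** (symptomatic, within the window, not from the target aneurysm).

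| Bleed | In the endpoint (7-1 with ISTH text)? | ISTH item on the form | Meets the hemorrhagic stroke definition? |
| --- | --- | --- | --- |
| Intracerebral or subarachnoid with objective signs | Yes | Redirected | Yes |
| Subdural or epidural | Yes, through ISTH | Redirected | No |
| Subarachnoid or intracerebral, headache only | Yes, through ISTH | Redirected | No |
| Isolated intraventricular | Yes, through ISTH | Redirected | Unclear; sites may code it either way |

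Rows two and three carry the point. The intraventricular row is weaker: the CT forms record the modified Fisher grade, which depends on intraventricular blood, so a new bleed of this kind can show as a change of grade.

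**Step 2: look for another place where the bleed would be caught.**

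- The CT forms (within 48 h and at day 14) ask about subarachnoid blood, parenchymal hematoma, hydrocephalus and drain-tract hemorrhage. They have no subdural or epidural field.
- Section 6 describes the independent review committee for the postoperative MRI outcome. The sections at hand describe no adjudication of bleeding; Section 22 was not among them.
- Monitoring (Section 15) is central and works from eCRF data.
- The details field of the stroke item and the open line for other adverse events could hold the bleed.

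**Step 3: direction and possible size.** The protocol states no bleeding rate, so there is no planned figure to reproduce. Assumptions for illustration:

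- n = 230 per arm (Section 14-2, before the dropout allowance)
- margin 0.10 (Section 14-3)
- true rates p_C = 0.10 and p_A = 0.20, so the true difference lies exactly on the margin and any non-inferiority claim is false
- a share s of events missed equally in both arms.

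Observed rates are c = p_C(1 − s) and a = p_A(1 − s). The observed difference is d = a − c, and SE = √[c(1 − c)/n + a(1 − a)/n]. The chance of claiming non-inferiority is Φ[(0.10 − d)/SE − 1.96].

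For s = 0.10: c = 0.09, a = 0.18, d = 0.09, and SE = √[(0.0819 + 0.1476)/230] = 0.0316. Then 0.01/0.0316 − 1.96 = −1.64, and Φ = 5.0%.

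| Share missed in each arm | Observed difference (points) | Chance of false non-inferiority |
| --- | --- | --- |
| 0% | 10.0 | 2.5% |
| 5% | 9.5 | 3.6% |
| 10% | 9.0 | 5.0% |
| 20% | 8.0 | 9.8% |
| 30% | 7.0 | 18.3% |

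The pattern depends only modestly on the assumed level. With 10% of events missed, the same formula gives 5.7% at true rates of 5% and 15% (c = 0.045, a = 0.135, SE = 0.0264), and 4.7% at 15% and 25% (c = 0.135, a = 0.225, SE = 0.0356).

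**The case against.** The best defence is that nothing leaves the endpoint. Section 7-1 joins its components with an or, ISTH major hemorrhage is one of them, and Section 8 includes ISTH events among the bleeding events. A narrow component beside a broad one is overlap. This stands. A reader might infer that subdural, epidural and headache-only bleeds are excluded from the outcome, and the documents do not support that.

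The form note can also be read as a guard against double entry. It says where to describe intracranial bleeding, not to omit it. The receiving item prints no anatomical limit, has a details field, and is backed by an open adverse event line. This stands in part: a sensible site may well record the bleed there. But it would be doing so against the protocol's own definition of the term on the item. An entry under other adverse events is not marked as an endpoint event, and an analysis plan cannot recover a bleed that was never entered.

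Drain-tract hemorrhage has its own CT item and, when symptomatic, is intracerebral, so it meets even the narrow definition. The concern about drainage in Section 1 is therefore partly covered already.

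A reader might further infer that the missed bleeds fall mostly in the aspirin arm and would reverse the result. The documents give neither bleeding rates nor the share of extra-axial bleeds, so this is unsupported. The argument does not need it, because equal loss in both arms already favours non-inferiority.

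**Conclusion.** Wrong as written, as an internal contradiction: the endpoint definition, the form note and the stroke definition cannot all be applied literally to a symptomatic subdural or epidural bleed or to a headache-only intracranial bleed. Such bleeds remain in key secondary outcome 1 by definition. The defect is a risk that they are not recorded, or are recorded differently from site to site, as endpoint events.

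The direction of the risk is towards non-inferiority. Its size cannot be derived from the protocol. The range of 3.6% to 9.8%, against a nominal 2.5%, rests on assumed true rates of 10% and 20%, on 5% to 20% of events being missed equally in both arms, and on 230 patients per arm. If extra-axial and headache-only bleeds are a very small share of all bleeds, or if sites use the free text consistently, the effect is negligible. The point should be corrected because it affects a safety claim and is cheap to settle.

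**What to change.** Reconcile 7-1 and the Section 8 definitions and event form in one of two ways: delete the note in brackets on the ISTH line, or relabel the receiving stroke item so that it takes any symptomatic intracranial hemorrhage not due to rupture of the target aneurysm, naming subdural and epidural bleeding.

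In either case, add one sentence to 7-1. It should state that key secondary outcome 1 counts every bleed meeting the ISTH critical-site criterion, whether or not it meets the definition of hemorrhagic stroke, and that the headache-only rule governs the stroke label alone.

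The cost is one form label and one sentence of definition. Events already entered as free text can be reclassified by someone blind to allocation. The reported bleeding rate may rise slightly.
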